### Recruitment

2.7

The patients will be recruited mainly through the outpatient and inpatient areas of the rehabilitation center of the First Affiliated Hospital of Henan University of Traditional Chinese Medicine, and we will use the Internet for online recruitment. The poster will briefly describe the trial and provide treatment details and contact details to eligible participants, and contact information. Participants who are interested in participating will be able to contact the researcher directly.

We will provide the potential participants with a detailed description of the benefits of the trial and acupuncture and the risks that may exist. If they decide to participate, they will be asked to sign the informed consent. Then, they will be included in this trial for randomization. If a participant withdraws from the trial, the reasons for withdrawal will be recorded.

In order to improve the patients compliance in the trial, we will strengthen the doctor-patient communication and the patient's health education timely, to increase the patients’ trust in members of the research group.

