### Primary outcome

4.1

We will use the Western Ontario and McMaster Universities Osteoarthritis Index (WOMAC) as the primary outcome measure.^[19]^ It consists of 24 items assessing the patients with KOA pain (5 items), stiffness (2 items) and physical function (17 items). The score ranges for the pain, stiffness and physical function subscales are, respectively, 0–50, 0–20 and 0–170, resulting in a total range of 0–240. Higher scores indicate more severe symptoms or physical disability. The evaluation will be performed at week 16 after randomization.

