### Statistical analysis

4.6

In this trial, we will implement the intention-to-treat analysis and per-protocol (PP) analysis. The intention-to-treat analysis will be used for all allocated participants in the baseline. This trial focuses on the long-term effect of acupuncture, and the observed data will be used as the primary analysis. Primary analysis will be based on intention-to-treat population, including participants with at least 1 assessment of the primary outcome and 1 acupuncture session. Per protocol (PP) analysis will be performed to test the robustness of the primary analysis. PP population will include participants receiving at least 12 sessions of acupuncture and be assessed at week 16.

The demographic and baseline characteristics among 3 groups will be compared using one-way analysis of variance (ANOVA). A χ^2^ test will be used for categorical variables. Due to the occurrence of self-healing tendency in KOA, it is important to testify the existence of the long-term effect of acupuncture effect. The clinical outcomes will be compared among the acupuncture with the *deqi* group, acupuncture without the *deqi* group and the waiting treatment group at every time points (week 0, 4th, 8th, 12th, 16th, 20th, and 24th after randomization) by using the repeated measures ANOVA (3 independent groups with repeated measures).

Clinical outcomes will be analyzed using SPSS 22.0 statistics software (IBM SPSS Statistics, IBM Corp, Somers, NY, USA). Data on Skewed distribution will be normalized. Means, standard deviations, and 95% confidence intervals (CIs) will be used to describe the continuous data. All statistical hypotheses are two-sided tests, and the significance test level α = 0.05, giving the test statistic and its corresponding *P* value, with *P* ≤ .05 as statistically significant. The data will be analyzed by statisticians who are blinded to the test settings. All confidence intervals will be two-sided 95% intervals among the 3 groups (group A, group B and group C).

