1.Recruitment of middle-aged and elderly patients with mild to moderate recurrent knee pain in the past month to avoid the impact of other diseases on pain assessment;2.In order to alleviate patients doubts about different interventions, patients in each group will be treated in different rooms, and patients in each group will be forbidden to talk.3.The acupuncturist is a doctor with more than 6 years of work experience and a medical practitioner certificate. Relevant personnel and data evaluators responsible for recruiting patients are required to undergo rigorous training before the study to ensure that all experimental procedures have uniform standards and avoid observational bias.4.Emotion monitoring. During the whole study, not only the emotional changes of patients will be evaluated on time by the emotion monitoring scales, but also the emotional changes of each patient should be paid close attention in order to eliminate the influence of emotional changes on the disease.

Of course, this study also has some shortcomings, mainly reflected in the following 2 aspects:

1.Because this study has a long observation period, it will result in a higher rate of abscission, which will affect the results of the study. Therefore, we should maintain a good doctor-patient relationship with patients during the study, and the part of the scales involved in this study are self-rating scale, which can be carried out subjectively by patients to better improve the quality of studys data;2.The patients enrolled in this study are limited to mild to moderate KOA patients, so the results of this study have some limitations, they may only be applicable to mild to moderate KOA individuals.

Most domestic and international medical treatment guidelines recommend acupuncture for knee osteoarthritis, but the long-term effect of acupuncture for KOA is not fully defined. Therefore, this study designs a clinical study with a treatment period of 4 weeks and a follow-up period of 20 weeks, aiming to study the long-term effect of acupuncture and the influence of the *deqi* sensation on the long-term in the treatment of KOA, and to provide a clinical basis for treatment of patients with mild to moderate knee osteoarthritis in clinic.

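### The per-protocol analysis named as the robustness test can show sensitivity to adherence but cannot reveal bias from patients lost by week 16

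*Protocol article*

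**What the plan says.** Four statements in the protocol article bear on this.

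- **Primary analysis (section 4.6).** The trial is about the long-term effect, and "the observed data will be used as the primary analysis". The primary population is called intention-to-treat and described as "including participants with at least 1 assessment of the primary outcome and 1 acupuncture session".
- **Robustness (section 4.6).** "Per protocol (PP) analysis will be performed to test the robustness of the primary analysis". The set is defined next: "PP population will include participants receiving at least 12 sessions of acupuncture and be assessed at week 16". The article names no other robustness or sensitivity analysis.
- **Primary time point (section 4.1).** For the primary WOMAC outcome: "The evaluation will be performed at week 16 after randomization". Section 4.2.1 adds WOMAC at six other times as a secondary outcome, and section 4.6 compares the groups over all seven times by repeated measures ANOVA.
- **Dropout.** The Discussion lists the long observation period as a shortcoming: "it will result in a higher rate of abscission, which will affect the results of the study". For those who leave, section 2.7 says: "If a participant withdraws from the trial, the reasons for withdrawal will be recorded". Sections 2.7 and 5 also describe efforts to retain patients through communication and trust.

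**The concern.** A robustness analysis is useful when it relaxes an assumption on which the primary result depends. Here that assumption is that patients with a week-16 value can stand for those without one. The PP set does not relax it, because a week-16 assessment is a condition of entry. What PP changes is adherence: it removes patients with fewer than 12 sessions.

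Loss could plausibly differ by arm. Patients are not blinded (section 2.5), patients are told about deqi before acupuncture (section 4.3), and the primary assessment comes 12 weeks after the 4-week treatment ends. If it does differ, the trial could report that PP confirms the primary result while both carry the same selection. The reader would take agreement as reassurance on a threat that the check never examined.

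**Working it through.** **Inputs from the protocol article.** Section 2.3 gives expected reductions in WOMAC total of 17 (A), 13 (B) and 8 (C), SD 10, α 0.05, power 0.90, 99 needed, one overall dropout rate of 10%, and 108 enrolled (36 per arm). The planned A−B difference is 17 − 13 = 4. Sections 4.1 and 4.6 give the time point and the analysis sets.

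**Assumed inputs, not in the article.** Loss by week 16 in each arm (p_A, p_B), and the gap δ by which leavers improve less than stayers. Among stayers, reaching 12 sessions is taken as unrelated to outcome.

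**Step 1: the plan's own figure.** One-way ANOVA with means 17/13/8 and SD 10 has power 0.899 at 32 per arm and 0.908 at 33 per arm. 3 × 33 = 99 reproduces, so these means and this SD are a fair base for illustration.

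**Step 2: who contributes at week 16.**

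| Patient | Observed-data week-16 comparison | Conventional repeated measures ANOVA | PP set |
|---|---|---|---|
| All visits present, 12 or more sessions | yes | yes | yes |
| All visits present, fewer than 12 sessions | yes | yes | no |
| Week 16 missing | no | no | no |

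The second row is what PP tests. The third row is the attrition question, and all three columns agree on it. A conventional ANOVA also drops patients who miss any other visit: with an assumed 3% missing independently at each of six post-baseline visits, 0.97^6 = 0.83 remain.

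**Step 3: effect on A−B.** In each arm, mean of all randomised = mean of stayers − p × δ. Hence

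expected observed A−B = true A−B + (p_A − p_B) × δ,

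and PP has the same expectation under the adherence assumption.

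| p_A | p_B | δ | Formula | Simulated primary / PP | 95% CI coverage |
|---|---|---|---|---|---|
| 10% | 25% | 10 | 4 + (0.10 − 0.25) × 10 = 2.5 | 2.47 / 2.47 | 91% |
| 25% | 10% | 10 | 4 + (0.25 − 0.10) × 10 = 5.5 | 5.51 / 5.51 | 91% |
| 10% | 25% | 5 | 4 + (0.10 − 0.25) × 5 = 3.25 | 3.25 / 3.26 | 94% |
| 10% | 10% | same in both arms | 4 + 0 = 4 | 3.98 / 3.99 | no material bias |

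The simulation used 36 per arm, SD 10, 8,000 trials and imperfect adherence in PP.

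**Step 4: the same point from the reader's side.** Suppose both analyses report A−B = 4.0. The difference among all randomised patients is then 4 − (p_A − p_B) × δ. For δ = 5, 10 and 15:

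- 20% lost in A, 10% in B: 3.5, 3.0, 2.5
- 30% v 10%: 3.0, 2.0, 1.0
- 10% v 20%: 4.5, 5.0, 5.5

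A separate simulation with 1,000,000 per arm gave matching observed-data and PP results to two decimals in every case, both about 4.0. Agreement at 4.0 is thus compatible with anything from 1.0 to 5.5 over these assumed values. The agreement is no empirical discovery: it follows from comparing nearly the same patients at one time point, and that is why it carries no information about the missing ones.

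**The case against.** **PP is a normal companion to intention-to-treat, and detailed missing-data methods belong in the analysis plan.** Both are fair. PP does vary adherence, from one session to 12, and section 4.6 does not claim that PP tests missing data. The analysis plan is not shown and may add more, so one cannot infer that no missing-data analysis exists. What stands is that the article itself gives the robustness role to PP, in a trial whose Discussion expects dropout to affect the results.

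**The primary set does not demand a week-16 assessment.** A reader might infer that both sets carry the same entry condition. The text does not say so: one assessment of the primary outcome is enough, and WOMAC is measured at seven times. The point rests instead on who supplies a week-16 value under observed data or under a conventional ANOVA.

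**The two analyses need not always agree.** If the repeated measures analysis were fitted by likelihood to all available visits, leavers' earlier scores would inform week 16. In a simulation with dropout driven by an earlier observed score (assumed correlation 0.8, loss 10% v 25%, leavers about 9 to 10 points worse), week-16 completers gave A−B of 2.8 and the likelihood analysis gave 4.0. So identical bias in every case is not supported. Even then PP is the more selected analysis, and it does not test whether dropout depends on unobserved outcomes.

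**The plan does not predict biased loss.** Correct. The Discussion predicts dropout that affects results, which may mean lost precision, and section 2.3 gives one overall rate of 10%. Retention efforts may also keep loss low, though they do not test its effect.

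**The A−C contrast.** It is tempting to extend the same shift to A−C. That cannot be assessed: group C receives no acupuncture during the trial (section 3.3), so the session conditions, read literally, exclude it from both sets.

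**Conclusion.** The concern holds in a limited form. The named robustness check can show sensitivity to adherence. It cannot reveal bias from who is lost by week 16, because it restores none of those patients. This rests on an observed-data week-16 comparison or a conventional repeated measures ANOVA; section 4.6 does not say how incomplete cases are handled.

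The size is conditional. With 10% v 25% loss and leavers 10 points worse, A−B shifts by 1.5 points, which is 1.5/4 = 38% of the planned difference. With equal loss and an equal gap it does not shift. The loss rates and gaps are assumptions, and the article gives no basis for choosing a direction. The documents do not show that the result will be biased. They show that agreement between PP and the primary analysis would not be evidence against such bias.

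**What to change.** In section 4.6:

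1. Describe PP as a secondary analysis of adherence, not as the robustness test of the primary result.
2. Name as the robustness test a week-16 missing-data sensitivity analysis on all randomised patients. One suitable form is multiple imputation of WOMAC using the earlier visits, with arm-specific delta shifts increased until the conclusion changes (the tipping point).
3. State that week-16 WOMAC is sought from patients who stop needling, so that fewer values have to be imputed. No particular mode of completion is proposed, since section 4.1 does not say that WOMAC is self-rated.
4. Reconcile the session conditions with the waiting-list group, so that A−C can be included in the same analysis.

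The cost is a few sentences, some follow-up effort and one extra analysis. The primary analysis can stay as it is. The downside is that the robustness statement may turn out less favourable than one based on PP.

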### Sample size

2.3

PASS was used for sample size determination. According to the previous study, WOMAC Function Score of KOA patients decreased by 12.1 points after acupuncture, by 9.4 points after sham acupuncture and 5.6 points after education, while WOMAC pain Score of KOA patients decreased by 3.6 points after acupuncture, by 2.6 points after sham acupuncture and 1.5 points after education.^[18]^ Based on the previous study and our clinical experience, we anticipated a reduction of WOMAC total score by 17 points after acupuncture with the *deqi* sensation, a reduction by 13 points after acupuncture without the *deqi* sensation and a reduction by 8 points in the wait-list control. With α = 0.05, 1 – β = 0.9, and a standard deviation of 10, we need at least 99 participants in total. Considering a dropout rate of 10%, a total of 108 participants will be included in this trial.

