#### Western Ontario and Mcmaster Universities Osteoarthritis Index (WOMAC)

4.2.1

The evaluation will be also performed at week 0, 4th, 8th, 12th, 20th, and 24th after randomization.

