The long-term effect of acupuncture which is an important feature of acupuncture treatment after cessation^[38]^ refers to the acupuncture effect that persists after the end of acupuncture treatment. Compared with immediate effect, the long-term effect is stronger, wider, more lasting and can be accumulated.^[39]^ Many studies have shown that the long-term effect is an important part of acupuncture that is different from placebo effect, and it is an important focus for improving the efficacy of acupuncture. It has been recorded in a lot of ancient Chinese medical books and reported in many kinds of clinical and animal trials. For example, acupuncture treatment for chronic tension-type headache,^[13]^ migraine,^[14]^ primary insomnia,^[15]^ tinnitus,^[16]^ chronic knee pain,^[40]^ rats with cerebral ischemia and reperfusion,^[41]^ etc. These studies have confirmed that the long-term effect is an important feature of acupuncture analgesia. However, the long-term effect is not clear about the efficacy of KOA. Therefore, in order to demonstrate the effectiveness of the *deqi* sensation on the long-term acupuncture effect in patients with knee osteoarthritis, we design a randomized controlled trial with a treatment period of 4 weeks and an observation period of 20 weeks to investigate and evaluate the long-term effect of acupuncture for KOA.

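### The only efficacy method named, a repeated-measures ANOVA over weeks 0 to 24, does not single out the week-16 WOMAC endpoint that the protocol makes primary

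*Protocol article*

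**What the plan says.** All references are to the protocol article.

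- **Primary outcome (4.1):** WOMAC, at one visit: "The evaluation will be performed at week 16 after randomization".
- **Secondary outcome, WOMAC (4.2.1):** the remaining visits: "The evaluation will be also performed at week 0, 4th, 8th, 12th, 20th, and 24th after randomization".
- **Statistical analysis (4.6):** one method for all clinical outcomes. The three groups are compared "at every time points (week 0, 4th, 8th, 12th, 16th, 20th, and 24th after randomization) by using the repeated measures ANOVA". Week 16 appears in this section only in that list and in the definition of the per-protocol population. The section does not say whether the group term or the group-by-time term decides, and names neither a week-16 contrast nor a baseline covariate.
- **Aim (4.6 and Discussion):** "This trial focuses on the long-term effect of acupuncture, and the observed data will be used as the primary analysis". The Discussion says that the long-term effect "refers to the acupuncture effect that persists after the end of acupuncture treatment". Treatment lasts four weeks (2.1).
- **Sample size (2.3):** one set of three mean reductions: 17 with deqi, 13 without deqi and 8 on the waiting list, with no visit attached. The calculation concludes: "With α = 0.05, 1 – β = 0.9, and a standard deviation of 10, we need at least 99 participants in total".

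**The concern.** The endpoint is a difference between groups at one visit, twelve weeks after treatment ends. The method gives two omnibus F tests across seven visits, and neither is that difference.

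- The **group term** compares averages over all visits. Week 0 is included, where randomisation makes the expected difference zero, and so is week 4, the end of treatment.
- The **group-by-time term** tests whether the group profiles are parallel. A divergence at any visit can make it significant.

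The six visits classed as secondary therefore carry the same weight in the test as the primary one. The question is whether benefit outlasts treatment, so an F test that an end-of-treatment difference can trigger does not answer it. Because no deciding term is named, the choice could be made after the data are seen. The error also runs the other way: a true week-16 difference can be diluted in the group term.

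**Working it through.** **1. The plan's own figure.** Inputs from Sample size: reductions 17, 13, 8; SD 10; α 0.05; power 0.90.

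Mean = 38/3 = 12.67. Sum of squared deviations = 4.33² + 0.33² + 4.67² = 40.67. Effect size f = √(40.67/3)/10 = 0.368.

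For a one-way ANOVA at a single time point, λ = n × 40.67/100 with 2 and 3n − 3 df.

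- n = 32: λ = 13.01, power 0.899.
- n = 33: λ = 13.42, power 0.908.

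The minimum is 33 × 3 = 99, exactly as stated. The trial was sized for a single-time-point comparison of three groups.

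**2. What the two omnibus terms see if the separation is at week 4 only.** Assumptions not in the document: SD 10 at every visit, complete data, equal correlation ρ between visits. Start from λ = 13.42.

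- Group term: the effect is averaged over 7 visits, so λ = 13.42 × (1/49) / [(1 + 6ρ)/7]. At ρ = 0.5 this is 0.48 on 2 and 96 df.
- Interaction: λ = 13.42 × (6/7) / (1 − ρ), on 12 and 576 df. This is 16.4, 23.0 and 38.3 at ρ = 0.3, 0.5 and 0.7, for power of 0.76, 0.91 and 0.995 without a sphericity correction.

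**3. Simulation** (3,000 trials per setting, 33 per arm, Greenhouse–Geisser correction for the interaction, one-way ANOVA at week 16). Proportion significant at 5%, separation at week 4 only:

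| Correlation | Interaction | Group term | Week-16 test |
|---|---|---|---|
| Equal, 0.3 | 73% | 10% | 5% |
| Equal, 0.5 | 90% | 8% | 5% |
| Equal, 0.7 | 99.5% | 7.5% | 5% |
| AR(1), 0.7 | 76% | 9% | 5% |
| AR(1), 0.85 | 97% | 8% | 5% |

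These agree with step 2. With no difference at any visit, each term is significant in about 4% to 6% of trials, so the high interaction rate comes from the week-4 difference and not from a faulty test.

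**4. The reverse case.** With the 17/13/8 separation at week 16 only, the group term detects it in 7% to 9% of trials. The week-16 ANOVA does so in 90% to 92%.

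**5. Sustained effect, ρ = 0.5.** The change score has variance 2 × 100 × (1 − 0.5) = 100, so its power is that of step 1, about 90% to 91%. Adjustment for baseline leaves variance 100 × (1 − 0.25) = 75, so λ = 13.42/0.75 = 17.9 and power is about 96% to 97% (96% simulated).

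**The case against.** **The method sentence may include a week-16 comparison.** It speaks of comparing groups at every time point, which can mean comparisons at each visit within the model. A reader might infer that the plan cannot test week 16 at all, and the text does not support that. On this reading a week-16 comparison exists, but as one of seven equal tests, one of them at baseline, and still not marked as primary.

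**Week 16 is already prespecified, and an analysis plan may supply the contrast.** The endpoint is indeed fixed in 4.1, and an unseen plan may add detail. But the point does not rest on silence: the article names a method, and that method does not match its own endpoint.

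**No false claim is written into the plan.** A reader might infer that the trial will declare a long-term effect whenever the interaction is significant. The article states no such rule. The 73% to 99.5% figures are rejection rates of one term, not rates of false conclusions, and the group term is much less affected.

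**The effect profile matters.** An effect that fades through weeks 8 and 12 would give similar or higher rates, but the Discussion defines the long-term effect as anything persisting after treatment, so those rejections would not all be false. Only the week-4-only profile is used here for that reason.

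**The SD of 10 may be that of change.** It stands beside anticipated reductions, so this is plausible. With SD 10 per visit the change SD is 10 × √[2(1 − ρ)]: 11.8, 10 and 7.7 at ρ = 0.3, 0.5 and 0.7. If the change SD is held at 10 under equal correlation, SD²(1 − ρ) is always 50 and the interaction λ is 23.0 whatever the correlation. The figure is then about 90%, and the value above 99% falls away. The conclusion does not change.

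**Week 0 as an outcome level is legitimate.** That stands. A contrast against week 0 is an unbiased change-score comparison, and it meets the planned power. Baseline adjustment is a gain in precision, not the repair of an error.

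**Conclusion.** The concern holds in this form: the stated analysis is not tied to the primary endpoint. Neither omnibus term is the week-16 difference, and the per-visit reading leaves week 16 undistinguished among seven. The sample size, in contrast, reproduces exactly from a single-time-point comparison.

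If the planned separation is present at week 4 and absent afterwards, the interaction is significant in about 90% to more than 99% of trials at equal correlation 0.5 to 0.7, and in about 73% at 0.3. The group term is significant in about 7% to 10%, and a week-16 test in about 5%. These figures assume 33 per arm, SD 10 per visit and complete data; the correlations are assumptions because the document gives none. The size varies with them, but the direction was the same in every setting tried.

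**What to change.** State in Statistical analysis that the primary test is the between-group comparison of WOMAC total at week 16, adjusted for baseline WOMAC total, with A–C and A–B contrasts at that visit. Either of two models serves:

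- an ANCOVA at week 16 with baseline as covariate; or
- the week-16 contrast from a mixed model on weeks 4, 8, 12, 16, 20 and 24, with group, visit, group-by-visit and baseline.

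The mixed model is an option and not a necessity. Label all other visits, and the omnibus group and group-by-time terms, as secondary. Testing the three groups jointly at week 16 before the two contrasts keeps the primary test in line with the sample-size calculation.

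The cost is a wording change in the protocol and any analysis plan, made before the data are unblinded. No new data are needed, since WOMAC is already collected at week 0, and the sample size is unaffected.

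### Week-0 WOMAC enters the model as one more outcome visit and not as a covariate, so the week-16 primary comparison is less precise than a baseline-adjusted one

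*Protocol article*

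**What the plan says.** Section 4.1 makes WOMAC the primary outcome and places its assessment at week 16. Section 4.2.1 adds the other visits: "The evaluation will be also performed at week 0, 4th, 8th, 12th, 20th, and 24th after randomization". A baseline value is therefore scheduled in every patient. Sections 4.2.2 to 4.2.4 do the same for KOOS, AIMS2-SF, BAI and BDI.

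Section 4.6 names one efficacy model. The clinical outcomes are compared among the three arms at "week 0, 4th, 8th, 12th, 16th, 20th, and 24th after randomization) by using the repeated measures ANOVA (3 independent groups with repeated measures". Week 0 stands in the list of outcome times, and no covariate is mentioned.

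Section 2.3 sizes the trial on reductions in WOMAC total: "With α = 0.05, 1 – β = 0.9, and a standard deviation of 10, we need at least 99 participants in total". It does not say whether the SD of 10 belongs to the change or to the score, and no section gives a correlation between visits.

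**The concern.** At week 0 treatment cannot yet have separated the arms, so a group comparison there tests chance alone. The useful role of the week-0 value is to explain part of the between-patient variation at week 16, and the named model does not give it that role. A raw week-16 comparison ignores baseline. A week-16 minus week-0 contrast uses it, but with a fixed slope of one in place of the estimated slope, which is less efficient whenever the correlation is below one.

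The trial is small. The deqi question rests on the smallest planned contrast, 17 − 13 = 4 points between groups A and B. Section 2.4 describes simple randomisation. If the baseline SD were also 10 (an assumption), a chance A versus B baseline difference at 36 per arm would have a standard error of 10 × √(2/36) = 2.4 points, more than half the planned effect. Baseline adjustment gains precision from data already being collected.

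**Working it through.** **Inputs**
- Mean drop in WOMAC total by arm, section 2.3: group A (deqi) 17, group B (no deqi) 13, group C (waiting list) 8.
- "With α = 0.05, 1 – β = 0.9, and a standard deviation of 10" (section 2.3); tests are two-sided (section 4.6).
- 99 evaluable patients at 1:1:1, so n = 33 per arm (sections 2.3 and 2.4).
- Baseline to week-16 correlation ρ: not stated. Assumed 0.5, with range 0.3 to 0.8.
- Reading of SD 10: not stated. Both readings are carried through.

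**1. Reproduce the plan's figure.** One-way F test with noncentrality λ = n·Σ(mᵢ − m̄)²/σ².
- m̄ = 38/3 = 12.67; the squared deviations are 18.78, 0.11 and 21.78, summing to 40.67.
- n = 33: λ = 33 × 40.67/100 = 13.42; on 2 and 96 df, power is 90.8%.
- n = 32: λ = 13.01; power is 89.9%.

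The smallest total reaching 90% is 99, as stated. It is the power of a single three-group comparison with no covariate.

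**2. A versus B without adjustment.** Noncentral t on the pooled 96 df: δ = 4/(10 × √(2/33)) = 4/2.462 = 1.625. Power is 36.3%.

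**3. Variance after adjustment.** With equal variance σ² at both visits, the raw score has variance σ², the change 2σ²(1 − ρ), and the baseline-adjusted score σ²(1 − ρ²). The adjusted variance is therefore:
- (1 + ρ)/2 times the variance of change, if SD 10 is the SD of change;
- (1 − ρ²) times the variance of the score, if SD 10 is the SD of the week-16 score.

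At ρ = 0.5 both factors are 0.75, so the adjusted SD is 10 × √0.75 = 8.66. One error df is deducted.
- Three-group test: λ = 13.42/0.75 = 17.89; on 2 and 95 df, power is 96.9%.
- A versus B: δ = 1.625/√0.75 = 1.876; power is 45.9%.

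**4. Range over ρ.** Unadjusted values are 90.8% and 36.3% throughout: a comparison of change on the left-hand reading, of the raw week-16 score on the right.

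| ρ | SD of change: adjusted SD | Three-group | A vs B | SD of score: adjusted SD | Three-group | A vs B |
|---|---|---|---|---|---|---|
| 0.3 | 8.06 | 98.5% | 51.4% | 9.54 | 93.3% | 39.2% |
| 0.5 | 8.66 | 96.9% | 45.9% | 8.66 | 96.9% | 45.9% |
| 0.7 | 9.22 | 94.8% | 41.5% | 7.14 | 99.7% | 61.5% |
| 0.8 | 9.49 | 93.6% | 39.6% | 6.00 | >99.9% | 76.4% |

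Every entry shows a gain. The A versus B gain is below 5 points at ρ = 0.3 on the score reading (39.2 − 36.3 = 2.9) and at ρ = 0.8 on the change reading (39.6 − 36.3 = 3.3).

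**5. Group main effect over all seven visits.** Assume compound symmetry, ρ = 0.5, no effect at week 0 and a constant effect afterwards. Each group difference in the seven-visit mean shrinks to 6/7, and the variance of that mean is 100 × (1 + 6 × 0.5)/7 = 57.14 (SD 7.56).
- Three-group test: λ = 33 × 40.67 × (6/7)²/57.14 = 17.25; power is 96.4%.
- A versus B: δ = (4 × 6/7)/(7.56 × √(2/33)) = 1.842; power is 44.6%.

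**The case against.** Several points against the concern carry weight.

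- **The gain has no single value.** A reader might infer that the plan gives up a fixed 6 points of three-group power and 10 points of A versus B power. Those differences arise only at ρ = 0.5, and the article states no correlation. Section 2.3 speaks of reductions, so the change reading is arguably the natural one; on it the gain shrinks as ρ rises.
- **Baseline is not wholly unused.** A reader might infer that chance imbalance is left in the result. With week 0 as a level of time, a week-16 minus week-0 contrast subtracts it. This also tempers the largest figure in the table: on the score reading at ρ = 0.8, a change comparison has SD 10 × √(2 × 0.2) = 6.32 and δ = 4/(6.32 × √(2/33)) = 2.57, giving 72.0% power against 76.4% adjusted.
- **The comparator is one visit, while the named model uses seven.** The seven-visit main effect comes close to the adjusted week-16 test at ρ = 0.5 (96.4% and 44.6%). That stands, but this effect averages over visits, does not target week 16, and is diluted by a visit with no possible effect.
- **Nothing is invalid.** Chance imbalance is already covered by the error rate of a randomised comparison, and the planned 90% three-group power is met without a covariate.
- **Covariates may be set in an analysis plan that is not shown.** Mere silence would be no finding. Here, however, section 4.6 gives week 0 an explicit role as an outcome time, and that role is what should change.

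**Conclusion.** The point holds as one of efficiency. Section 4.6 places week-0 WOMAC among the outcomes, and a week-16 comparison on the raw score or on change is less precise than one adjusted for baseline. At 33 per arm and an assumed ρ of 0.5, power would rise by 96.9 − 90.8 = 6.1 points for the three-group test and 45.9 − 36.3 = 9.6 points for A versus B. Both figures depend on ρ and on what SD 10 measures, and should be read with the table. They apply to a single week-16 comparison and not to every test in the repeated measures ANOVA. The calculation assumes equal variances at the two visits.

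A reader might also infer that adjustment would rescue the deqi comparison. It would not: A versus B power is still below 50% at ρ = 0.5. The weakness comes mainly from sizing the trial on the three-group test.

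**What to change.** In section 4.6, take week 0 out of the outcome vector. Compare week-16 WOMAC total among the arms by ANCOVA on group plus week-0 WOMAC total, or by the week-16 contrast of a longitudinal model with week-0 WOMAC as covariate. Treat KOOS, AIMS2-SF, BAI and BDI the same way, each with its own week-0 value. Fix this before unblinding, so that the choice to adjust cannot appear to depend on the results.

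The cost is one sentence of wording and one residual degree of freedom. No further patients, visits or data are needed, and the planned SPSS software fits ANCOVA.
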